### 3.3. Ethical Considerations

The protocol has been developed according to the Good Clinical Practice guidelines of the International Conference on Harmonization (ICH) and of the Declaration of Helsinki principles. The Ethical Committee of the National Cancer Institute of Naples, Italy approved it with document no. 88/20. Written informed consent will be obtained before starting the collection of blood samples and SRT. The structure that has the responsibility for registration, collection, and management of personal data will protect the privacy of patients included in the PRELUDE-1 study. A progressive numerical code will be attributed to the patients to manage documents, electronic data systems, or communications. A list with numerical codes and associated patients’ names will be kept exclusively at the secretariat of the PRELUDE-1 study. Only the Ministry of Health or Ethics Committees can know patients’ names (as required by the current legislation) for inspection and control purposes. 

The choice to treat two or three nodules with SRT was based on scientific, practical, and ethical considerations that deserve to be briefly described. The mainstay treatment of one nodule is surgery; moreover, abscopal effect cannot be detected in this context. On the other hand, four nodules are not consistent with the definition of oligo-metastatic disease we adopted [4,5]; in this case, a front-line systemic treatment is more appropriate. However, SRT will be applied only if the largest nodule measures ≤25 mm and the sum of all nodules is ≤7 cm. A strict monitoring of non-irradiated nodules will be performed already after two months in order to treat those with SRT in case of progression. However, chemotherapy is allowed at any time after the first radiologic assessment and liquid biopsy post-SRT according to multidisciplinary discussion and the European Society of Medical Oncology (ESMO) guidelines. The independent ethical committee approved the protocol after reassurance on these specific aspects.

### 3.4. Liquid Biopsy and Sequencing

For liquid biopsies, blood samples will be collected in streck-cell-free DNA BCT^®^ (pluriSelect Life Science, [name]) tubes and centrifuged at 1800× *g* for 10min. Thereafter, plasma will be further centrifuged at 3000× *g* for 10min, aliquoted, and stored at −80°C prior to analysis. The QIAamp DNA Blood Mini Kit (Qiagen, Hilden, Germany) will be used to extract circulating free (cfDNA). Formalin-fixed and paraffin-embedded (FFPE) tissue specimens of primary lesions will be collected and ten μM serial sections cut from each tissue specimen for microdissection of tumor cells under morphological control. DNA isolation will be performed through the MGF03-Genomic DNA FFPE One-Step Kit (MagCoreDiatech, RBCBioscience, [name]). Tumor DNA quality from PEFF tissues will be established using the FFPE QC Kit according to the manufacturer’s protocol (Illumina, San Diego, CA, USA). Concentration, quantity, and integrity of cfDNA will be assessed through a 2100 BioAnalyzer (Agilent Technologies, Santa Clara, CA, USA) to determine the size distribution of cfDNA fragments. DNA libraries for tumor genetic evaluations will be obtained with TruSigt Oncology (TSO) 500 kit, based on gene-target enrichment that analyzes 523 cancer-relevant genes (see Supplementary File for the complete list of genes). The assay reveals small nucleotide variants (SNVs), indels, splice variants, as well as tumor mutational burden (TMB) and microsatellite instability (MSI) as immunotherapy biomarkers. Sequencing will be performed on an Illumina NovaSeq 6000 (San Diego, CA, USA) platform. 

### 3.5. Tumor-Infiltrating Lymphocytes Analysis in Primary CRC

Immunohistochemistry (IHC) will be applied to analyze T cell subsets in the tumor microenvironment. Briefly, formalin-fixed, paraffin-embedded 4-μm tissue sections of primary CRC will be stained according to a biotin-streptavidin-peroxidase method (YLEM kit, Rome, Italy) previously described [9]. Primary antibodies to characterize lymphocyte subpopulations will be anti-human CD3, anti-human CD8, anti-human FoxP3, and anti-human Granzyme B [76]. Finally, immune-stained slides will be counterstained with hematoxylin, dehydrated, and mounted in Diatex. Substituting the primary antibody with a mouse myeloma protein of the same subclass at the same concentration as the monoclonal antibody will represent the negative controls. An automated scanning microscope and image analysis system (Genetix, San Jose, CA) will be used to scan the slides. Two expert pathologists ([name] and [name]) blinded to all clinical information will review all qualitative and quantitative analyses of T-cell subsets. The tumor contexture will be divided into tumor core (TC) and invasive margins (IM) as previouslydescribed [77]. T-cell subsets densities (cells/mm^2^) results will be depicted through the arithmetic averages + 2 standard deviations (SD). 

### 3.6. HLA Allele Haplotype Determination

HLA haplotypes at loci A, B, C, and DRB1 will be assessed centrally at the University of Campania “L. Vanvitelli” through a low-medium-resolution reverse SSO DNA typing assays (One-Lambda Luminex Technology LABScan 100, HLA Fusion Software) on genomic DNA extracted according to the kit manufacturer from whole blood or peripheral blood mononuclear cells. Comparisonof the results with our database bank including healthy bone marrow donors (Campania National Registry) will be performed.

### 3.7. Cytokines Determination

Blood samples will be collected from a peripheral vein at the decided times during the treatment courses and kept on ice. Serum will be aliquoted and stored at −80 °C until analyzed after centrifugation (3000 r.p.m. for 10 min at 4 °C). An ELISA-based immunoassay, using monoclonal antibodies specific for the different target proteins will be used. Multiple soluble cytokines will be assessedwith either commercially or customized kits: Interferon (IFN)γ, TNFα, IL-4, IL-8, IL-10, IL-12, IL-17, vascular endothelial growth factor (VEGF), granulocyte colony-stimulating factor (G-CSF), angiopoietin-2, and hegapocyte growth factor(HGF). Each experiment will be performed in duplicate. Serum levels of all proteins will be determined using a multiplate reader (Biorad, Hercules, CA, USA), and the substance concentration will be assessedthrougha standard curve, with software provided by the manufacturer (BioRad Manager Software, Hercules, CA, USA).

### 3.8. Bioinformatics Analysis and Data Presentation

An IlluminaTruSigth Oncology bioinformatics pipeline will be used to analyze DNA sequencing results. Number of reads and coverage in the target regions will be required to be above the manufacturer’s suggested thresholds. Sequence data will be aligned to the human reference genome GRCh37 (http://www.ncbi.nlm.nih.gov/projects/genome/assembly/grc/human/index.shtml) (accessed on 22 June 2021) through the Burrows–Wheeler Aligner with default parameters [78]. GENCODE, ICGC-PCAWG, dbNSFP, COSMIC, ClinVar, CancerMine, 1000Genomes, OncoScore, CIViC, and CBMDB databases will be used to assess the clinical significance of the found variants. The global minor allele frequency cut-off to filter and remove variants will be <1%. The four-tiered structure, designed by the joint consensus recommendation of the AMP/ACMG [79] will be applied to prioritize variants. However, to exclude residual false positives, variants will be also manually curated. The overall genetic evolution will be indicated with: (i) the percent of mutational concordance between different samples and (ii) Venn diagrams in order to plot intersections among genetic results in different samples (see beyond). Phenolyzer, a computational tool that prioritizes genes on the basis of updated existing knowledge (protein–protein interactions, the sharing of biological pathways or gene families, gene–gene transcriptional regulation, etc.), will be used to evidence relevance and relationships between any “seed” genetic variants and “secondary” ones [80]. 

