### 2.5. Definition of “Genetic Regression”

In a previous study in lung-limited omCRC, we documented changes of KRAS status in metastatic formalin-fixed and paraffin-embedded (FFPE) tumor tissues compared to the primary ones (KRAS was mutated in primary tumor but not in subsequent metastases) [9]. These genetic trajectories were associated with a good prognosis as observed also in omCRC with liver-limited disease [65] and poly-metastatic CRC [66]. Therefore, we defined “genetic regression” as the loss of the genetic alterations in a specific key-driver gene from the primary tumor to the metastatic one (i.e., mutant KRAS (mutKRAS) in primary tumor→wild-type KRAS (wtKRAS) in metastases). This issue was opposed to “progressive” genetic trajectory (i.e., wtKRAS in primary tumor→mutKRAS in metastases) where the metastatic lesions gain genetic alterations advantageous for the tumor development [67]. RAS proteins (specifically, KRAS and NRAS) are small GTPases along the epidermal growth factor receptor (EGFR) pathway [68,69]. When activated by ligand/receptor binding, RAS protein releases GTP, binds to GTP, and, in turn, activates crucial kinases(i.e., RAF proteins, phosphoinositide 3-kinase (PI3K)-AKT, etc.) involved in several cancer-related phenomena (migration, survival, adhesion, growth, and differentiation) [70]. These data indicate that omCRC tumor clones may follow regressive genetic trajectories differing from those of cancer cells with poly-metastatic behavior.

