## 3. Trial Design

### 3.1. Objectives

#### 3.1.1. Primary Objective

The primary objective is to verify that SRT can induce regression of KRAS mutant clones into the entire metastatic mass in a clean model of oligo-metastatic CRC. 

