### 3.2. Design and Sample Size Calculation

PRELUDE-1 is a prospective, translational, and proof-of-principle study to detect regression of KRAS mutations in CRC induced by SRT. It will be conducted at the academic hospital Istituto Nazionale Tumori di Napoli, IRCCS “G. Pascale” in Naples (Italy). The sample size of the PRELUDE-1 study is based on the innovative hypothesis that radiation-induced immunity could induce regressive trajectories in metastases bearing KRAS oncogene mutations (i.e., mutKRAS→wtKRAS). 

According to the binomial test, considering a frequency of KRAS mutations of 50.0% (the study is not restricted to KRAS mutated patients) and assuming a probability of mutKRAS→wtKRAS of p_0_ = 0.0077 [9], with α = 0.05, 1-β = 0.60, p = the *a priori* success rate, and X = the number of patients with mutKRAS→wtKRAS, the final sample size is 25 patients. With the algorithm $P\left(X,N,p\right)=\left(\begin{array}{c} N\\ x \end{array}\right)p^{x}{\left(1-p\right)}^{n-x}$, the regressive trajectory is statistically relevant if mutations occurs in >2 out of the planned 25 patients.

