### 3.12. Response and Toxicity Assessment

Response will be assessed through total-body computed tomography (CT) with iv contrast (if contraindicated: abdomen MRI and high-definition chest-computed tomography without iv contrast), CEA, CA19.9, and PET-FDG after 40 days from the end of SRT. A CT scan will be repeated at two months and, thereafter, every three months until progression. RECIST v. 1.1 (https://recist.eortc.org/recist-1-1-2/) (accessed on 22 June 2021) will be applied to classify responses. An independent and blinded data monitoring committee (DMC) will review radiologic responses. The DMC will also review the PFS data. Toxicity will be evaluatedaccording to the CTCAE, version 4.0 (https://www.eortc.be/services/doc/ctc/CTCAE_4.03_2010-06-14_QuickReference_5x7.pdf) (accessed on 22 June 2021). The presence of eventual adverse events will be evaluated at each study visit. Patients will also notify the investigator by telephone in case of adverse events occurring between one visit and the next. The maximum grade per patient will be reported for each adverse event. A toxic effect of any grade on multiple occasions will be counted only once.

FDG-PET will be performed after 40 days from the treatment end to early monitor untreated nodules. In this case, tumor metabolic changes will be evaluated according to the European Organization for Research and Treatment of Cancer (EORTC) criteria [81,82]. Metabolic responses by FDG-PET/CT are defined as follows: Complete metabolic response (CMR), complete resolution of all metabolically active target and non-target lesions, and no new lesions;Partial metabolic response (PMR), 20% or greater decrease in SUV of target lesions with or without decrease in number/size of nontarget lesions, and no new lesions;Progressive metabolic disease (PMD), one or more new lesions, 20% or greater increase in SUV of target lesions, and/or unequivocal increase in FDG activity of nontarget lesions;Stable metabolic disease (SMD): not qualifying as CMR, PMR, or PMD.

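### KRAS calls that decide the primary endpoint pass through a discretionary, exclusion-only curation step with no stated fixed KRAS rule or masking to time point

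*Protocol article*

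**What the plan says.** All references are to the protocol article.

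- **Primary objective (3.1.1):** "The primary objective is to verify that SRT can induce regression of KRAS mutant clones into the entire metastatic mass".
- **Decision rule (3.2):** "the regressive trajectory is statistically relevant if mutations occurs in >2 out of the planned 25 patients". I read this as three or more patients with mutKRAS→wtKRAS. The null probability p0 is 0.0077, α is 0.05, and KRAS mutation frequency is put at 50%, with enrolment not restricted to KRAS-mutated patients.
- **Variant calling (3.8):** one pipeline with read and coverage thresholds, a population-frequency filter, database annotation and tiering. After that: "However, to exclude residual false positives, variants will be also manually curated". The article gives no criterion for this step, no number of readers and no masking.
- **Samples (3.4, 3.11, Table 1):** tissue from the primary tumor, plasma at baseline (LB-T1), and plasma 40 days after SRT (LB-T2). The study ends after LB-T2.
- **Blinding stated elsewhere:** in 3.5 the pathologists are "blinded to all clinical information will review all qualitative and quantitative analyses of T-cell subsets", and in 3.12, "An independent and blinded data monitoring committee (DMC) will review radiologic responses". The first is a tertiary readout and the second a secondary one.
- **Definition of regression (2.5):** "loss of the genetic alterations in a specific key-driver gene from the primary tumor to the metastatic one". It does not name the liquid biopsy pair.

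**The concern.** In most trials, over-strict removal of positive calls is conservative. Here the event of interest is a variant that is no longer called, so a step that only removes calls can itself produce the event. A true KRAS call removed at LB-T2 moves a KRAS-mutant patient to mutKRAS→wtKRAS. A true call removed from the earlier sample makes that patient unable to show regression, but it does not cancel a false success in someone else.

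The trial is judged on three events against an expectation well below one, so a few removals could carry the result. As written, the step leaves the removal of a KRAS call to judgement, and a reader of the results could not tell regression from curation. The article states protection for two lesser readouts and none for this one.

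**Working it through.** **Inputs.** From 3.2: N = 25, p0 = 0.0077, threshold 3 or more, α = 0.05, KRAS frequency 50%. The number who can show regression is 25 × 0.50 = 12.5, taken as 12 (13 is also shown). The wrongful-removal rate f is assumed. The documents give no value.

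**Step 1: the plan's own rule.** The expected count under the null is 25 × 0.0077 = 0.19. The exact tail is P(X ≥ 3) = 1 − [P(0) + P(1) + P(2)] = 1 − [0.8243 + 0.1599 + 0.0149] = 0.0009. On the stated null, three events would almost never arise by chance, so any other source of events dominates the error rate. The sample size of 25 itself cannot be reproduced because no alternative rate is given. That does not bear on this point.

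**Step 2: true KRAS calls removed at LB-T2 only.** Each of n KRAS-mutant patients becomes a false success with probability f, so X ~ Binomial(n, f). True regression is set to zero.

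| f (assumed) | Expected false successes, n = 12 | P(X ≥ 3), n = 12 | P(X ≥ 3), n = 13 |
|---|---|---|---|
| 2% | 0.24 | 0.0015 | 0.0020 |
| 5% | 0.60 | 0.020 | 0.025 |
| 10% | 1.20 | 0.111 | 0.134 |
| 20% | 2.40 | 0.442 | 0.498 |

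Worked for f = 10%, n = 12: 1 − (0.2824 + 0.3766 + 0.2301) = 0.111.

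**Step 3: the same removal rate at LB-T1 and LB-T2, independently.** A false success now needs the call kept at LB-T1 and dropped at LB-T2, so its probability is f(1 − f).

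| f (assumed) | f(1 − f) | Expected false successes, n = 12 | P(X ≥ 3), n = 12 | P(X ≥ 3), n = 13 |
|---|---|---|---|---|
| 5% | 0.0475 | 0.57 | 0.017 | 0.021 |
| 10% | 0.09 | 1.08 | 0.087 | 0.105 |
| 20% | 0.16 | 1.92 | 0.30 | 0.35 |

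**Step 4: what the two tables show.** Removal that is even-handed across time points lowers the chance of a false positive trial only modestly. Masking alone would therefore leave most of this exposure in place, and a fixed KRAS rule is needed as well. In both tables the chance is below 0.05 at f = 5% and above it at 10%. If the primary tumor rather than LB-T1 is the reference, removals at LB-T1 give no offset and Step 2 applies.

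**The case against.** **A reader might infer that curation is unblinded.** The documents do not say so. Section 3.8 is silent, and coding, masking and batching of samples are details that a condensed article can leave to laboratory procedures; 3.13 refers to institutional operating procedures. This part of the objection stands. The point is only that masking is not stated.

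**A reader might take the probabilities as the size of assessor bias.** They are not. They contain no blinding term, and Step 3 shows that most of the effect survives even-handed removal. This stands too.

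**The removal rates have no basis in the documents.** This also stands. Curation follows an automated pipeline with several filters, and nothing suggests that it would discard 5% to 20% of true KRAS calls. At 5% or less the illustrated chance stays below α.

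**Curation covers all samples, so it is not one-way.** Correct: removal from the primary tumor or LB-T1 reduces the number at risk. But it only partly offsets false successes at LB-T2, as Step 3 shows.

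**The deciding pair is not fixed.** Section 2.5 speaks of primary tumor to metastasis, and no section names LB-T1 and LB-T2 as the endpoint pair. The use of LB-T2 is therefore an inference, but a firm one, because no other post-SRT liquid biopsy is scheduled.

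**One dropped call does not make the trial positive.** True: one gives one success, and three are needed.

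What the objections leave untouched is that 3.8 itself writes a discretionary exclusion step, without a stated rule, into the calls behind the primary endpoint. That is a choice the article makes, and a better method is available at little cost.

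**Conclusion.** The point holds as a weakness in how the primary readout is fixed, not as a demonstrated error or evidence of bias. KRAS calls are open to discretionary removal, absence of the call after SRT is the success event, and the article states neither a fixed KRAS rule nor masking to time point for that step.

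The size is conditional. With 12 KRAS-mutant patients and no true regression, an assumed 10% wrongful-removal rate gives a 0.11 chance of meeting the rule if removal occurs at LB-T2 only, and about 0.087 if it is equal at both plasma samples. The stated null gives 0.0009. At 5% the figures are 0.02 and 0.017. These rest on independent patients, 50% KRAS frequency, LB-T2 as the deciding sample, and rates that are mine to assume. The change is worth making because it costs almost nothing and protects the one result on which the trial is judged.

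**What to change.** In 3.8:

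1. Take KRAS out of discretionary curation. For any KRAS variant found in the primary tumor or at LB-T1, report the read count and depth at that position in LB-T2, and call it present or absent by one pre-set rule applied identically to both plasma samples.
2. State that any remaining manual curation is done on coded samples, masked to patient and time point.

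The cost is protocol wording and sample coding. Section 3.4 already has plasma aliquoted and stored at −80 °C before analysis, so no new patient procedure is needed. The small downside is that KRAS results wait for the later sample if the pair is called together.

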### 3.9. Eligibility Criteria

Inclusion criteria. 

Cytological or histological diagnosis of colorectal adenocarcinoma.Two or three asymptomatic lung metastases smaller than or equal to 25 mm.Age <80 years.ECOG performance status of 0 or 1.Available FFPE resected primary tumor.Negative pregnancy test for all potentially childbearing women.Written informed consent.

Exclusion criteria. 

Previous systemic anti-tumor treatments or radiotherapy interrupted at least 6 months before.Neutrophils <2000/mm^3^ or platelets <100.000/mm^3^ or hemoglobin <9 g/dL; serum creatinine level> 1.5 times the maximum normal value; bilirubin level >3 times the maximum normal value; AST and/or ALT >5 times the maximum normal value.Previous or concomitant malignant neoplasms (excluding basal or spinocellular cutaneous carcinoma or in situ carcinoma of the uterine cervix).Active or uncontrolled infections.Cardiovascular diseases including coronary artery disease (CAD), inadequately controlled hypertension, ischemic or hemorrhagic stroke, moderate/sever arrhythmias, aortic aneurysm requiring surgical repair, recent deep vein thrombosis with or without pulmonary embolisms, moderate/sever valvular heart diseases, recent arterial thrombosis.Other uncontrolled or uncompensated diseases (diabetes, asthma, chronic obstructive pulmonary disease, etc.).Refusal or inability to provide informed consent.Impossibility to guarantee follow-up.

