### 2.4. Rationale for Evaluating Genetic Evolution of Cancer through Liquid Biopsies

The cancer genome is highly heterogeneous and dynamic. Mutation gains in some genes prompt cancer progression and resistance to therapy. Study of these changes is crucial to understand cancer biology and to propose innovative treatments. The most direct method to assess cancer genetics relies on the sampling of tumor tissues and its molecular characterization through whole genome sequencing techniques [55,56]. However, some issues can limit these evaluations since (i) biopsies are invasive and cannot be easily repeated during the treatments, (ii) tumor tissue is not always available, (iii) the genetic fingerprint of the neoplasia can change during the time due to the clonal selection of the host environment and to the different treatments. Alternatively, liquid biopsy is a non-invasive method to characterize cancer DNA, which can be repeated over time and which can collect circulating cancer material coming from all the clones of the neoplasia [57]. The technique is based on assessing tumor DNA released into the blood of cancer patients. In fact, it is well known that at least three cancer-associated phenomena concur to enrich the blood flow of tumor DNA: apoptosis, cell necrosis, and active secretion. Therefore, circulating tumor DNA (ctDNA) represents the tumor fingerprint in the blood. Next-generation sequencing (NGS), whose complete dissertation is beyond the scope of this study, is a suitable and reliable tool for genetic characterization through liquid biopsy in CRC [58,59]. 

Identifying the genetic and immunologic evolutions of cancer, in time and space, is a new and challenging issue. The introduction of high-throughput genetic assessments including NGS has enormously prompted this aspect of cancer research. Such an approach is providing novel and unexpected insights in cancer biology and suggesting new therapeutic strategies. Many studies in pmCRC have revealed heterogeneous results in the genetics of primary tumors (PT) and “matched” metastatic lesions (as evidenced by the occurrence of *de novo* mutations) with concordance rates (shared point mutations/total number of point mutations) ranging from 0 to 100% [60,61,62,63,64]. 

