#### 3.1.2. Secondary Objectives

The most important secondary objective is the description of eventual radiologic responses in non-irradiated disease (abscopal effect). It will be measured through total-body computed tomography (CT) with iv contrast (if contraindicated: chest-computed tomography without iv contrast).

Other secondary objectives are the responses’ duration, progression-free survival (PFS), and toxicity (see beyond for response and toxicity assessment criteria). The response duration will be measured from the time of documented objective response until documented tumor progression. PFS will be determined from the data of treatment start until progression. Overall survival is generally long in this clinical setting so that it cannot be evaluated in the short time of the study. 

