### 3.11. Timing of Exams and Procedures

Timings and types of procedures are synthesized in Figure 1 and Table 1.

Screening phase. Inclusion and exclusion criteria will be evaluated during the screening phase.

Baseline phase. Thereafter, after signing the informed consent, a venous blood sample (10 mL) for the liquid biopsy (LB) will be collected coinciding with the routine assessment before the SRT start. Baseline visit (clinical history, clinical examination, PS ECOG, vital signs) and exams (including basal LB (LB-T1)) will also be carried out within 14 days before the SRT start. Blood count and clinical biochemistry will be performed at our local laboratories. The following parameters will be assessed: blood count with leukocyte formula, hemoglobin, platelets, total bilirurbin, AST, ALT, alkaline phosphatase, serum creatinine, total proteins, sodium, potassium, calcium, urea, lactic dehydrogenase, creatinine clearance, CEA, and CA19.9. Patient’s heart rhythm and conduction will be evaluated with ECG. The ventricular ejection fraction will be assessed with cardiac ultrasonography.All potentially childbearing women musthave a negative pregnancy test during the screening phase. If requested by the local ethics committee, the test can also be repeated during treatment. Barrier methods for anti-conception must be used by all patients throughout the duration of the study. FDG-PET and total-body computed tomography with iv contrast or, if contraindicated, magnetic resonance (MRI) abdomen and high-definition chest-computed tomography without iv contrast will be performed. 

Treatment phase. Clinical examination and evaluation of vital signs will be performed at each radiotherapy visit. Cardiological evaluation, CEA, CA19.9, and assessment of response to treatment will be performed after 40 days and 2 months from the radiotherapy start and, thereafter, every 3 months until progression. 

“Interval” phase. LB-T2 will be performed 40 days after major nodule irradiation coinciding with post-RT cell blood count and biochemical assessment along with CT total-body-scan and FDG-PET. Thereafter, the disease will be monitored every three months, and non-irradiated nodules will be treated in case of volumetric progression according to clinical practice in oligo-metastatic disease.

End-of-study phase. The study ends after LB-T2 assessment. 

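### The prior-treatment exclusion runs backwards on its plainest reading and allows a second reading that enrols different patients

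*Protocol article*

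**What the plan says.** Under the exclusion heading of Section 3.9, the first item is "Previous systemic anti-tumor treatments or radiotherapy interrupted at least 6 months before". The inclusion list in the same section covers histology, number and size of lung lesions, age, performance status, available primary tumor tissue, pregnancy test and consent. It says nothing about earlier treatment.

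Other sections bear on how that item should be understood:

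- Section 3.1.1 sets out to verify that "SRT can induce regression of KRAS mutant clones into the entire metastatic mass in a clean model of oligo-metastatic CRC".
- Section 3.1.2: "The most important secondary objective is the description of eventual radiologic responses in non-irradiated disease (abscopal effect").
- Section 2.4 gives as one limit of tissue sampling that "the genetic fingerprint of the neoplasia can change during the time due to the clonal selection of the host environment and to the different treatments".
- Section 3.3 states that "chemotherapy is allowed at any time after the first radiologic assessment and liquid biopsy post-SRT".
- Section 3.11 fixes the baseline: "exams (including basal LB (LB-T1)) will also be carried out within 14 days before the SRT start". The second liquid biopsy (LB-T2) follows 40 days after irradiation of the largest nodule.

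**The concern.** An item in an exclusion list names the patients who are kept out. This one names patients whose treatment stopped at least 6 months earlier. Taken at its word, it keeps out those with the longest treatment-free interval and lets in those with the shortest.

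That sits badly with the rest of the design. The primary objective calls for a clean model and assigns the genetic change to SRT. The article accepts that treatments alter tumor genetics. It holds chemotherapy back until the first scan and liquid biopsy after SRT. The period just before the baseline sample has no matching protection.

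The article describes no comparison group. Each patient is compared with himself or herself, before and after SRT. If another treatment is still acting when the baseline sample is drawn, its effect and that of SRT cannot be separated in circulating tumor DNA, cytokines, regulatory cells or non-irradiated nodules.

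**Working it through.** No figure in the article depends on this criterion, so the check is of wording and logic.

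**Step 1: list the readings.** The 6-month clause can attach to both kinds of treatment (reading A, the plainest) or to radiotherapy alone (reading B, under which any previous systemic treatment excludes). The table also shows what would follow if the line were a treatment-free requirement placed under the wrong heading (reading C). That is a plausible slip, but the article does not say so.

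| Last treatment | Reading A | Reading B | Reading C |
|---|---|---|---|
| Systemic, ended less than 6 months ago | not excluded | excluded | excluded |
| Systemic, ended 6 months ago or longer | excluded | excluded | not excluded |
| Radiotherapy, ended less than 6 months ago | not excluded | not excluded | excluded |
| Radiotherapy, ended 6 months ago or longer | excluded | excluded | not excluded |

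A and B differ in one row: recently ended systemic treatment. They agree on radiotherapy, where recent treatment is admitted and remote treatment barred. C differs from A in all four rows and from B in three.

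**Step 2: look for a rule elsewhere that settles it.** The rest of Section 3.9 has none. Section 3.3 concerns chemotherapy after SRT. Section 3.11 and Table 1 fix when assessments are made, not how long a patient must have been off treatment. No other part of the article sets an interval before SRT.

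**Step 3: ask what literal use would do to the endpoints.** The genetic event is a change from mutant to wild-type KRAS. Section 2.5 defines regression from primary tumor to metastasis, while the schedule also supplies LB-T1 and LB-T2. The effect of carry-over depends on the comparison and on timing:

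- LB-T1 against LB-T2, with mutant DNA already cleared by earlier treatment before LB-T1: the patient cannot show a later change, so carry-over adds no success.
- LB-T1 against LB-T2, with clearance still under way after LB-T1: the change is counted and may be credited wrongly to SRT.
- Primary tumor against a liquid biopsy: clearance caused by earlier treatment can be counted as regression.

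The sign of any bias is therefore not fixed, and its size would need the number of recently treated patients and their clearance rates, neither of which the document gives. What follows without those figures is weaker attribution to SRT.

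**The case against.** The strongest reply is that this is a drafting slip which one academic center would not apply against the purpose of its own trial. Section 1 presents SRT as a way to postpone more toxic therapy. Section 3.3 allows chemotherapy only after the first post-SRT scan and liquid biopsy, which implies that none is given between the two samples. Reading B also keeps out patients with recent systemic treatment.

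Much of this stands. A reader might infer that the trial admits recently treated patients and that its endpoints are contaminated. The document does not establish that: it shows a written rule that permits it on one reading, or for radiotherapy only on the other. The reply does not rescue the text, however. Section 3.3 does not reach the time before LB-T1, and the radiotherapy half is reversed on both readings, in a study of radiation-induced immunity.

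Two further inferences should be resisted.

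- *That two or three carry-over cases would decide the primary test.* Section 3.2 requires more than 2 of 25, so at least three. Each must first be KRAS-mutant, which the plan assumes for half of the patients (25 × 0.5 = 12.5), and Step 3 shows that carry-over need not create a success.
- *That patients with disease outside the lung could enter and inflate the result.* The Simple Summary, the Abstract and Section 2.3 name the population as lung-limited. Mutant DNA shed by such deposits would tend to hide a change to wild type, not produce one.

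**Conclusion.** The criterion is wrong as written and should be corrected. It is reversed for both kinds of treatment on the plainest reading and for radiotherapy alone on the other, and no other text resolves the choice. Because it is an operative enrolment rule, literal compliance would select patients who fit the study's stated aim poorly.

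The consequence is a risk to attribution, with no number attached. It rests on three points: the before-after comparison without a control group, a baseline sample close to SRT, and the article's own statement that treatments change tumor genetics. It also assumes that the line is applied as printed, which cannot be known from the document.

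**What to change.** The sponsor should reconcile the item in Section 3.9 with Sections 2.4, 3.1.1 and 3.3. Two things need stating: the intended direction of the 6-month interval, and whether it applies to systemic treatment, to radiotherapy or to both. The line should then be reworded so that only one reading is possible. Which rule is intended is for the sponsor to say.

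The cost is a one-line clarification, with no new procedure. Enrolment may be slightly narrower if recently treated patients were being accepted.
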